#### Chart abstraction

Clinical information will be abstracted from the patient’s medical record at baseline (at time of study enrollment), during treatment(s), and following completion of any treatment(s). Clinical and treatment data collected through chart abstraction is summarized in Table 3. Treatment data will include dates of treatment, procedural details (stenting, esophagectomy, gastrostomy tube placement), radiation treatment regimens, chemotherapy regimens, major treatment- and disease-related complications, best response to treatment (if evaluated), reasons for discontinuing treatment or pursuing supportive care, and date and cause of death. Data will be collected on the time elapsed from diagnosis to initiation of treatment to account for any treatment delays that may explain differences in survival during analyses.

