#### Exploratory endpoints

Exploratory endpoints related to processes of care will also be measured, including time from presentation to initiation of ESCC treatment, time to deliver intervention (defined as total time elapsed from initiation of treatment to last day of treatment), and total number of days hospitalized during and after an intervention. Measures of healthcare utilization that will be assessed include hospitalization events (total number of times hospitalized and cumulative days hospitalized), and the proportion of patients receiving a subsequent intervention for recurrent or persistent dysphagia. Hospitalization is defined as admittance to the inpatient setting of a hospital (medical or surgical ward or intensive care unit) for a period of ≥24 h per participant report.

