### Data collection procedures

#### Case report forms (CRFs)

CRFs are comprised of both medical chart abstraction instruments and standardized questionnaires. CRFs collect socio-demographic details (including age, sex, ethnicity, location of permanent residence, highest level of education completed, self-reported annual household income, health insurance status), baseline clinical information, treatment-related data, as well as vital status and QOL metrics over long-term follow up (see Table 3).

**Table 3 Tab3:** Data collected during TOEC-Eastern Africa study

Collected data	Baseline	Prior to treatment	During treatment	Follow up^**a**^
Sociodemographic				
Age	x			
Sex	x			
Ethnicity	x			
Occupation	x			
Location of permanent residence	x			
Highest level of education completed	x			
Annual household income	x			
Health insurance status	x			
Smoking and alcohol use	x			
Clinical data				
Medical History	x			
HIV status (date of and last CD4 count, use of antiretrovirals)	x			
Date/method of diagnosis	x			
Histopathological data (if applicable)	x			
Endoscopic findings (location/length of tumor)	x			
Imaging (if applicable)^b^	x			
Use of opiate medications for pain control	x	x		x
Hospitalizations			x	x
Vital status (including cause of death, if applicable)			x	x
Treatment				
Prior EC treatment (if applicable)	x			
EC treatment received, including delays/interruptions in treatment and reasons			x	
Complications			x	
Response assessment (if applicable)			x	
Quality of life				
Modified Rosenblatt Index^c^	x	x		x

*EC* Esophageal cancer

^a^Follow up assessments performed 1 month after initiation of treatment, 3 months after initiation of treatment, and then every 3 months until death or loss to follow up

^b^Any imaging modality performed during baseline assessment, including chest x-ray, ultrasound, computed tomography, positron emissions tomography, etc.

^c^The Modified Rosenblatt Index assesses the following: Dysphagia, Odynophagia, ‘Chest and/or Back pain,’ WHO performance status, and ‘Overall Well-being’ since starting treatment

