Cochran-Armitage test will be used to compare symptom metrics assessed using the ‘Modified Rosenblatt Index’ (Dysphagia, Odynophagia, ‘Chest and/or Back pain,’ WHO performance status, and ‘Overall Well-being’ since starting treatment) between each of the different palliative EC treatments (chemotherapy, radiotherapy, chemoradiation, esophageal stenting, basic supportive care) at each time point: 1 month after initiation of treatment, 3 months after the initiation of treatment and then every 3 months thereafter. We will also test for within-subject differences in scores between baseline (or pre-treatment) and each of post-treatment time points by McNemar’s Chi-squared test. In addition, generalized estimating equations (GEE) framework will be applied to analyze this longitudinal QOL data, where the treatment will be considered as the fixed effect and the subject-specific effects are the random effects.

Complications will be summarized as number of patients (%) with 95% confidence intervals and compared between treatment arms by Chi-squared test. Among palliative interventions, secondary outcome measures related to dysphagia will be compared using log-rank test and cph models to adjust covariates, including age, sex and baseline clinical covariates. ‘Time to achieve any dysphagia relief’ will be defined as time from treatment to improvement in dysphagia score of greater than or equal to 1. ‘Duration of dysphagia relief’ will be defined as time elapsed after treatment with any improvement in dysphagia from baseline. ‘Dysphagia-adjusted survival’ will be defined as the total time period with a dysphagia score of 0 to 2.

Measures of healthcare utilization and process measures related to the delivery of ESCC treatment by treatment approach will be examined as exploratory endpoints. Time-to-event measures will be compared among treatment groups by log-rank test. Count of hospitalization events, and total number of days hospitalized during and after ESCC treatment will be compared among treatment groups by ANOVA (or Kruskal Wallis test when normality assumption is not held). Chi-squared test will be used to compare the need for subsequent intervention for recurrent or persistent dysphagia by treatment approach. All analyses will be performed overall and within each site.

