Palliative interventions for EC have been an active area of research over the last several decades. Most of this research has taken place in HICs, with several RCTs having investigated best practices for palliation among patients with either ESCC or esophageal adenocarcinoma [9]. These studies highlight the tradeoffs between esophageal stenting with SEMS and the use of radiation-based therapies in patients with advanced disease [22, 23]. SEMS have been shown to provide immediate dysphagia relief, but are prone to failure over time due to stent migration and/or recurrent obstruction. Radiation-based therapies, including external beam therapy (EBRT) with or without chemotherapy and brachytherapy, have delayed effects, but may offer more durable symptom control. Steyerberg et al. developed and validated a prognostic index to help guide treatment selection in this patient population, with the rationale that SEMS may be advantageous for those with short life expectancies [24]. Subsequent efforts to evaluate this index in a South African patient population found that it had poor predictive value in this context, highlighting the challenges of generalizing evidence from clinical trials in HICs to low resource settings [25]. Advanced dysphagia, severe weight loss, and malnutrition are all much more prevalent among patients with EC in these settings. Access to supportive care is often more limited as well. These differences, both in terms of patient characteristics and health system factors, underscore the importance of advancing research on treatment strategies for ESCC in sub-Saharan Africa, with the goal of optimizing treatment delivery in this context. Although RCTs remain the gold standard in comparative effectiveness research, several challenges emerge with this study design in Eastern Africa, including the ethics of randomizing patients who are often in poor general condition, and the time, infrastructure and resources needed for implementing well-designed clinical trials [26, 27].

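### Table 3 and the chart-abstraction text disagree on whether complications and treatment are recorded after treatment ends; if Table 3 governs, the safety comparison rests on unequal observation windows

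*Protocol article*

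**What the plan says.** All references are to the protocol article.

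- **Chart abstraction.** Clinical information is taken from the medical record at enrolment, "during treatment(s), and following completion of any treatment(s". Serious complications, whether due to treatment or to disease, are listed among the treatment data with no event window. The section names Table 3 as the summary of what is abstracted.
- **Table 3** ("Data collected during TOEC-Eastern Africa study") has four time columns: baseline, prior to treatment, during treatment, follow-up. The rows "EC treatment received, including delays/interruptions in treatment and reasons" and "Complications" each carry one mark, under during treatment. The row "Hospitalizations" and the vital-status row are marked under both during treatment and follow-up.
- **Patient interviews.** Contacts after enrolment are by mobile phone and are described as covering vital status and quality of life.
- **Secondary endpoints.** Major complications and treatment-related mortality are named.
- **Statistical methods.** "Complications will be summarized as number of patients (%) with 95% confidence intervals and compared between treatment arms by Chi-squared test". No time window is attached.
- **Exploratory endpoints.** One measure is "the proportion of patients receiving a subsequent intervention for recurrent or persistent dysphagia".
- **Discussions.** Stents "are prone to failure over time due to stent migration and/or recurrent obstruction".

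**The concern.** Safety is one of the three outcomes that the study objectives name for comparing treatments. The planned summary counts patients with complications, so it depends on how long each patient is observed. Read literally, the during-treatment column gives a stent patient an observation window of one procedure and a radiotherapy or chemotherapy patient a window of the whole course. The article itself says that stents fail later. Stenting is also the largest expected group, at 1102 of 2476.

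Two things are at stake. First, six sites could follow different readings of the schedule, so that ascertainment differs by site as well as by treatment. Second, events that were never collected cannot be recovered at analysis, however the window is later defined. The same blank cell leaves it unclear where later interventions for dysphagia are recorded, although the article plans to compare treatment groups on them.

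**Working it through.** The article states no complication rate, so there is no figure of its own to reproduce. The check is a reading of the schedule, followed by an illustration with assumed rates.

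**Step 1: the two schedules side by side.**

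| Item | Table 3, during treatment | Table 3, follow-up | Chart abstraction text |
|---|---|---|---|
| Complications | marked | blank | listed, no window; clinical information also abstracted after completion |
| Treatment received | marked | blank | as above, covering any treatment(s) |
| Hospitalizations | marked | marked | not listed |
| Vital status | marked | marked | date and cause of death listed |

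The table separates the two periods for hospitalizations and vital status, so a blank follow-up cell can fairly be read as intended. The text says abstraction continues after treatment and then defers to a table that shows no such collection for these two rows. That post-treatment abstraction includes complications is a reasonable inference; the text does not say so outright.

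**Step 2: is there another collection route?** The follow-up interviews are described as covering vital status and quality of life. Hospitalization means an inpatient stay of at least 24 h by participant report, so a shorter re-intervention visit would not count. The quality-of-life index scores the severity of dysphagia, not whether a stent has migrated or blocked. None of these replaces a complication record.

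**Step 3: what a literal Table 3 could do.** Group sizes are from the Sample size section: stenting 1102; radiotherapy with or without chemotherapy 464 + 212 = 676. The true risk *p* and the share *f* of complications that occur after treatment ends are assumptions; the article gives neither. If late events go unrecorded,

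observed risk = *p* × (1 − *f*).

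With *p* = 20% in both groups, so that there is no true difference:

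| Late share, stent / radiotherapy | Observed stent | Observed radiotherapy | Risk ratio | Probability of p < 0.05 |
|---|---|---|---|---|
| 50% / 20% | 0.20 × 0.50 = 10% | 0.20 × 0.80 = 16% | 0.62 | 0.96 |
| 30% / 30% | 14% | 14% | 1.0 | 0.05 |
| 20% / 50% | 16% | 10% | 1.6 | 0.955 |

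The last column is the power of a two-sided two-proportion test at 0.05. For the first row:

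- pooled proportion = (1102 × 0.10 + 676 × 0.16) / 1778 = 0.1228
- standard error under no difference = √[0.1228 × 0.8772 × (1/1102 + 1/676)] = 0.0160
- standard error under the observed rates = √(0.09/1102 + 0.1344/676) = 0.0167
- power = Φ[(0.06 − 1.96 × 0.0160) / 0.0167] ≈ Φ(1.71) ≈ 0.96

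For the 50% / 20% shares, the probability is 0.72 at a true risk of 10% and above 0.99 at 30%.

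Unequal late shares alone can therefore produce a significant difference where none exists, but the sign follows the late shares, which the article does not give.

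**The case against.** The strongest reply is that the columns of Table 3 need not be literal calendar windows. Its footnote counts follow-up from initiation of treatment, so the 1-month contact can fall inside a course of radiotherapy or chemotherapy, and the columns overlap. Response assessment is also marked only under during treatment, yet the text abstracts best response, which is not confined to that period. The columns may instead separate treatment data taken from charts from data taken by interview. On that reading late complications in the chart are abstracted, and a repeat stent is simply a new treatment, since the text speaks of treatments in the plural. Late failure also shows up elsewhere: dysphagia is scored at each follow-up contact, hospitalizations are recorded at follow-up, and duration of dysphagia relief is a secondary outcome. Finally, a complication window may well be set in an analysis plan that is not shown.

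Much of this stands. A reader might infer that late stent failures are missed and that the safety comparison favours stenting. The documents do not support that as fact. Late events are lost only if Table 3 governs, late complications of radiotherapy and chemotherapy would then be lost too, and no late-event shares are given for any treatment. Nor can it be said that later interventions have no collection point; it is only unclear where they are recorded.

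What the reply does not remove is the conflict itself. The chart-source reading is also an inference, the text defers to the table, and an analysis plan can define a window but cannot supply events that sites did not collect. The absence of a stated window is therefore not the finding; the contradictory collection schedule is.

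**Conclusion.** The inconsistency between Table 3 and the Chart abstraction section is real and bears on a named secondary safety endpoint. Its consequence is conditional. If sites follow Table 3, observation windows differ by treatment and the Chi-squared comparison may be biased. A bias toward stenting is plausible given the late stent failure that the Discussion describes, but its direction and size are not established. In the illustration, an equal 20% risk could be recorded as 10% against 16% in either direction, or without distortion, according to the assumed late shares. If sites follow the text, the problem largely falls away. The forms themselves are not shown, so which reading operates in practice is unknown. The point is worth correcting because the correction is cheap and the loss, if it occurs, cannot be repaired at analysis.

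**What to change.** - Reconcile the two places: in Table 3, mark the complications row and the treatment-received row under follow-up, and state that the latter includes re-intervention.
- Check that the forms in use at all six sites agree with the corrected table.
- Compare complications over one common window counted from treatment start for every treatment group, for example to the 1-month and 3-month contacts.

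Follow-up calls and chart abstraction are already planned, so the cost is a few extra questions per call, some added abstraction and a sentence in the analysis section.

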#### Data management

Data will be first collected using paper forms with subsequent entry of de-identified data into Research Electronic Data Capture (REDCap™), a secure web-based application for data storage. All study-related information, including completed paper forms for study participants, will be stored in locked cabinets in a secure location only accessible to authorized study personnel at each study site. Data for each participating site will be stored within a password-protected REDCap™ data access group, with access limited to only authorized personnel from the recruiting AfrECC site. Electronic data capture forms within REDCap™ include data entry fields with programmed checks (‘validation rules’) for range and structure. University of California, San Francisco (UCSF) will serve as the data management coordinating center; however, each site will have access to its own data through this open-source platform.

### Sample size

We aim to recruit all patients with ESCC based on histological confirmation or presumptive clinical diagnosis that meet the eligibility criteria at participating AfrECC sites. We forecast a total accrual of an estimated 2476 study participants across all six sites (see Table 1) over the duration of the study. This estimate is based on annual ESCC cases observed in recent case series at KCH (unpublished data), annual recruitment to a recent case-control study at KCMC [18], as well as annual accrual rates in the present study at ORCI, MNH, and Tenwek since study initiation (Tenwek Hospital, *n* = 220 study participants per year; ORCI, *n* = 130 per year; and MNH, *n* = 150 per year). Of the total study population, we estimate 1102 study participants will be treated with esophageal stenting, 145 with chemotherapy, 464 with radiotherapy, 212 with concurrent chemoradiation, 450 with supportive care alone, and 103 with esophagectomy. Based upon previous data that indicate median OS following stenting is 36 weeks [10], radiotherapy with or without chemotherapy is 27 weeks [13, 19], and chemotherapy is 14 weeks [5, 19], our primary analysis comparing OS of different palliative interventions for ESCC will have the following power to detect differences between each pairwise comparisons based upon alpha of 0.0167 (adjusting for 3 comparisons based on Bonferroni correction): stenting vs. radiotherapy with or without chemotherapy, power = 0.99; stenting vs. chemotherapy, power = 1.00; and radiotherapy with or without chemotherapy vs. chemotherapy, power = 1.00.

### Statistical methods

All patients consenting to study participation with a histopathologically-confirmed or clinical diagnosis of EC will be included in the analyses. Descriptive statistics will be used to describe the proportion of ESCC patients receiving treatment with each modality at participating AfrECC sites. We will assess the associations between demographic/clinicopathologic characteristics and the treatment modalities employed (chemotherapy, radiotherapy, chemoradiation, esophageal stenting with SEMS, esophagectomy, supportive care alone). Categorical variables and continuous variables will be compared among the groups using Pearson’s Chi-squared test, and Analysis of Variance (ANOVA) (or Kruskal Wallis test when normality assumption is not held), respectively. Possible transformation (e.g., logarithm transformation) will be performed if the data is skewed.

OS will be defined in two ways: 1) from the date of initial diagnosis to the date of death or last patient contact; and 2) from date of initiation of treatment to date of death or the date of last patient contact. Kaplan-Meier method will be used to summarize OS and log-rank test will be used to compare survival curves among treatments overall and stratified by the study center. Furthermore, Cox proportional hazards (cph) modeling will be used to account for demographic and clinicopathological factors by including them as covariates. Proportionality of hazards for key covariates will be tested by examining the correlation between time and scaled Schoenfeld residuals and log-log plots of survival. Important covariates that violate the proportionality assumption will be used to stratify the cph model. In many settings in Eastern Africa, long delays can occur between diagnosis and initiation of treatment. To mitigate immortal time bias that can emerge in time-to-event analyses of observational studies, two analytical approaches will be employed. First, in analyses using OS defined by date of diagnosis, the time from diagnosis to the initial treatment will be added as a covariate. Secondly, in analyses of associations between different treatments and OS, treatment status will be included in Cox regression modeling as a time-varying covariate (defined as treated versus untreated). This approach allows for patients to accrue follow up time while awaiting treatment, while also accounting for any events that occur during the ‘untreated’ waiting period [20]. Our primary analysis will examine pairwise comparisons of: stenting vs. radiotherapy with or without chemotherapy, stenting vs. chemotherapy, and radiotherapy with or without chemotherapy vs. chemotherapy. Among patients receiving radiation, outcomes may differ between patients receiving radiotherapy alone as compared to concurrent chemoradiation. Exploratory analyses will examine these subgroups separately.

Cochran-Armitage test will be used to compare symptom metrics assessed using the ‘Modified Rosenblatt Index’ (Dysphagia, Odynophagia, ‘Chest and/or Back pain,’ WHO performance status, and ‘Overall Well-being’ since starting treatment) between each of the different palliative EC treatments (chemotherapy, radiotherapy, chemoradiation, esophageal stenting, basic supportive care) at each time point: 1 month after initiation of treatment, 3 months after the initiation of treatment and then every 3 months thereafter. We will also test for within-subject differences in scores between baseline (or pre-treatment) and each of post-treatment time points by McNemar’s Chi-squared test. In addition, generalized estimating equations (GEE) framework will be applied to analyze this longitudinal QOL data, where the treatment will be considered as the fixed effect and the subject-specific effects are the random effects.

Complications will be summarized as number of patients (%) with 95% confidence intervals and compared between treatment arms by Chi-squared test. Among palliative interventions, secondary outcome measures related to dysphagia will be compared using log-rank test and cph models to adjust covariates, including age, sex and baseline clinical covariates. ‘Time to achieve any dysphagia relief’ will be defined as time from treatment to improvement in dysphagia score of greater than or equal to 1. ‘Duration of dysphagia relief’ will be defined as time elapsed after treatment with any improvement in dysphagia from baseline. ‘Dysphagia-adjusted survival’ will be defined as the total time period with a dysphagia score of 0 to 2.

Measures of healthcare utilization and process measures related to the delivery of ESCC treatment by treatment approach will be examined as exploratory endpoints. Time-to-event measures will be compared among treatment groups by log-rank test. Count of hospitalization events, and total number of days hospitalized during and after ESCC treatment will be compared among treatment groups by ANOVA (or Kruskal Wallis test when normality assumption is not held). Chi-squared test will be used to compare the need for subsequent intervention for recurrent or persistent dysphagia by treatment approach. All analyses will be performed overall and within each site.

All statistical analyses will be performed using Stata or R statistical software. The significance level will be set for 0.05 for all analyses and multiple testing adjustments will be performed by Bonferroni correction.

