**Methods:**

This prospective, observational, multi-center, open cohort study aims to describe the therapeutic landscape of ESCC in Eastern Africa and investigate the outcomes of different treatment strategies within the region. The 4.5-year study will recruit at a total of six sites in Kenya, Malawi and Tanzania (Ocean Road Cancer Institute and Muhimbili National Hospital in Dar es Salaam, Tanzania; Kilimanjaro Christian Medical Center in Moshi, Tanzania; Tenwek Hospital in Bomet, Kenya; Moi Teaching and Referral Hospital in Eldoret, Kenya; and Kamuzu Central Hospital in Lilongwe, Malawi). Treatment outcomes that will be evaluated include overall survival, quality of life (QOL) and safety. All patients (≥18 years old) who present to participating sites with a histopathologically-confirmed or presumptive clinical diagnosis of ESCC based on endoscopy or barium swallow will be recruited to participate. Key clinical and treatment-related data including standardized QOL metrics will be collected at study enrollment, 1 month following treatment, 3 months following treatment, and thereafter at 3-month intervals until death. Vital status and QOL data will be collected through mobile phone outreach.

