## Background

Esophageal cancer (EC) is one of the leading causes of cancer morbidity and mortality worldwide. Most recent estimates from GLOBOCAN report that EC is the eight most common cancer globally with 604,000 annual incident cases and the sixth leading cause of cancer-related mortality with 544,000 deaths each year [1]. Nearly 80% of all EC cases occur in low- and middle-income countries (LMICs), where esophageal squamous cell carcinoma (ESCC) is the dominant histology [2]. Incidence rates for ESCC exhibit substantial geographic variation globally with several regions impacted by a disproportionately high burden of this disease. Eastern Africa has been identified as one of these geographic “hot spots,” along with north-eastern Iran, Central Asia, north-central China, and southern South America [2, 3]. In Eastern Africa, EC is the fifth leading cause of cancer mortality [1], with ESCC comprising 90% of cases [4].

Limited research has been published on the treatment of ESCC in sub-Saharan Africa [5]. In this setting, more than 90% of patients present with advanced or inoperable disease, and few are candidates for treatment with curative intent [6–8]. Palliative treatment strategies for advanced ESCC thus dominate the therapeutic landscape and include stenting for malignant obstruction with self-expandable metallic stents (SEMS), radiotherapy, chemo-radiotherapy, and brachytherapy. Use of each of these treatment modalities is supported by data that originates from high-income countries (HICs) [9]. The unique challenges of delivering care in resource-constrained settings, however, limit the generalizability of these findings to many African settings. In a previous systematic review of all studies on EC treatment in Africa [5], we identified only four prospective case series evaluating treatment of advanced ESCC in Eastern Africa, three of which reported outcomes of palliative stenting at two sites in Kenya and Malawi [10–12] and one that reported outcomes of palliative radiation in Ethiopa [13]. To date, no study has prospectively compared treatment modalities for advanced ESCC in Eastern Africa. Furthermore, little is known regarding the impact of different ESCC treatments on patients’ quality of life (QOL) in this setting. Of all the studies identified in our prior systematic review, only one examined QOL as an outcome metric [13].

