## Methods

### Study objectives

The goals of the TOEC-Eastern Africa study are:To describe the treatment patterns for ESCC at referral hospitals in Eastern Africa.To investigate the outcomes of different ESCC treatments in Eastern Africa, specifically overall survival, QOL, and safety, with a particular focus on palliative interventions including chemotherapy, radiotherapy with or without chemotherapy, esophageal stenting with SEMS, and supportive care.To examine process measures related to the delivery of ESCC treatment at referral hospitals in Eastern Africa, including time from presentation to initiation of treatment, total time to deliver an intervention, and total number of days hospitalized during and after ESCC treatment.To assess utilization of healthcare resources by ESCC treatment approach, as measured by hospitalization events (total number of times hospitalized and cumulative days hospitalized) and need for subsequent intervention for recurrent or persistent dysphagia.

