### Eligibility criteria

Patients aged ≥18 years with a diagnosis of EC will be eligible for study inclusion. Expanded inclusion criteria will be used as not all patients with suspected EC undergo diagnostic biopsies due to the costs associated with biopsy and pathological review. Diagnostic criteria for EC will include either histopathological confirmation or clinical diagnosis based on barium swallow (esophagram) and/or upper endoscopy without biopsy. This clinical criteria has been shown to have a > 90% pre-test probability for the diagnosis of ESCC in Eastern Africa [17]. Access to a mobile phone is not a requirement for study entry; however, should a study participant lack access, this will be noted on baseline enrollment forms. Patients who have previously received treatment for EC will be eligible for study participation; in these cases, details of prior EC treatment will be abstracted from medical records, if available.

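### Eligibility and the analysis set cover esophageal cancer of any histology, while the aims and primary comparison are stated for squamous cell carcinoma (ESCC)

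*Protocol article*

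**What the plan says.** Two sections of the protocol article use EC without restriction on histology.

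- Eligibility criteria: "Patients aged ≥18 years with a diagnosis of EC will be eligible for study inclusion". The diagnostic rule that follows does not require squamous type: "Diagnostic criteria for EC will include either histopathological confirmation or clinical diagnosis based on barium swallow (esophagram) and/or upper endoscopy without biopsy".
- Statistical methods, first sentence: "All patients consenting to study participation with a histopathologically-confirmed or clinical diagnosis of EC will be included in the analyses".

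Other sections state the population as ESCC.

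- Abstract, Methods: adults with a "histopathologically-confirmed or presumptive clinical diagnosis of ESCC based on endoscopy or barium swallow will be recruited to participate".
- Study objectives: "To investigate the outcomes of different ESCC treatments in Eastern Africa, specifically overall survival, QOL, and safety".
- Sample size: "We aim to recruit all patients with ESCC based on histological confirmation or presumptive clinical diagnosis that meet the eligibility criteria". The same section describes the primary analysis as a comparison of palliative interventions for ESCC.
- Statistical methods, second sentence: the treatment shares are to be described among ESCC patients, directly after the set has been fixed as EC.

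The Background keeps the two terms apart for Eastern Africa, "with ESCC comprising 90% of cases", and the Discussion names ESCC and adenocarcinoma as separate diseases. Table 3 lists histopathological data, where applicable, among the baseline items.

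**The concern.** No sentence says what happens to a patient whose biopsy shows a histology other than squamous. Under the eligibility and analysis-set sentences, that patient is enrolled and analysed, and the result is reported under an ESCC objective. Under the abstract and sample size wording, the patient is outside the target population. Two analysts working from this text could build different primary sets.

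The reason given for broad entry is that biopsy and pathology review cost money, so some patients have none. The clinical criterion is supported by a probability of ESCC above 90%. That argument covers patients without a biopsy. It does not cover patients whose biopsy has ruled ESCC out.

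At stake is whom the treatment-pattern proportions, survival contrasts and quality-of-life comparisons describe. A secondary issue is confounding. Table 1 ties treatment to site: ORCI has external-beam radiotherapy but no stents or endoscopy, while Tenwek and MNH have stents but no radiotherapy. If histology differed by site, the difference could carry into stenting versus radiotherapy.

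**Working it through.** **1. The plan's own figures.** Site forecasts: 862 + 476 + 472 + 253 + 320 + 93 = 2476. Treatment groups: 1102 + 145 + 464 + 212 + 450 + 103 = 2476. Both match the stated total.

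The power inputs come from the Sample size section: stenting 1102, radiotherapy with or without chemotherapy 464 + 212 = 676, chemotherapy 145; median survival 36, 27 and 14 weeks; alpha 0.0167. Exponential survival gives hazard ratios of 27/36 = 0.75, 14/36 = 0.389 and 14/27 = 0.519.

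Formula (Schoenfeld): power = Φ(|ln HR| × √(D × p × (1 − p)) − z), where D is the number of deaths, p the share in one group, and z = 2.394 for a two-sided 0.0167. The article states neither sidedness nor event counts, so two-sided testing and the following death counts are assumptions:

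- Administrative censoring only: event fraction 1 − [exp(−λF) − exp(−λ(A + F))]/(λA), with λ = ln 2/median, uniform accrual A = 47 months and minimum follow-up F = 6 months. This gives 0.849 for stenting and 0.903 for radiotherapy.
- 70% of patients die under observation.
- 50% of patients die under observation.

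For stenting versus radiotherapy, p = 1102/1778 = 0.620. With administrative censoring, D = 1102 × 0.849 + 676 × 0.903 ≈ 1546, and power = Φ(0.2877 × √(1546 × 0.2357) − 2.394) = Φ(3.10) = 0.999. With 70% events (D = 1245), power is 0.994. The stated 0.99 is reproduced. The other two comparisons give 1.00 in both scenarios, as stated.

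**2. How many patients could be affected.** Taking the regional 90% share to hold in this cohort, 0.10 × 2476 = 247.6, about 248, leaving 2476 − 248 = 2228. If spread evenly (an assumption), that is about 110 stented patients (0.10 × 1102), 68 irradiated (0.10 × 676) and 14.5 given chemotherapy (0.10 × 145). With an assumed 5% share the total is about 124. These counts include patients without a biopsy, who cannot be identified. The article does not give the number biopsied.

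**3. Power after restriction to 90% of each group.**

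| Stenting vs radiotherapy | Deaths, all EC | Power, all EC | Deaths, 90% set | Power, 90% set |
|---|---|---|---|---|
| Administrative censoring only | 1546 | 0.999 | 1392 | 0.998 |
| 70% events | 1245 | 0.994 | 1120 | 0.989 |
| 50% events | 889 | 0.962 | 800 | 0.940 |

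In the 90% set, stenting versus chemotherapy stays at 1.00 throughout. Radiotherapy versus chemotherapy is 1.00 in the first two scenarios and 0.992 with 50% events.

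**The case against.** The strongest reply is that the article uses the two terms loosely. Its title says esophageal cancer, the recruitment section moves from EC to ESCC within a paragraph, and the Sample size sentence can be read as ESCC patients who also meet the entry criteria. On that reading, biopsy-proven adenocarcinoma was never meant to be in the cohort. This stands to the extent that the text does not prove a deliberate choice to analyse other histologies as ESCC. It does not remove the conflict, because the analysis-set sentence still says otherwise.

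A second reply is that the Cox models adjust for demographic and clinicopathological factors, which may include histology, and that the covariate list may sit in a fuller document. That weakens the confounding argument. It does not define the target population. It also does not reach the analyses that carry no such adjustment: the Kaplan-Meier curves, log-rank tests, treatment proportions, and the chi-squared and Cochran-Armitage tests.

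A third reply is that other remedies are valid, such as restating the aims for EC and stratifying or adjusting by histology. That is fair. It would be consistent, but it would give up the ESCC-specific conclusions on which the article is built.

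**Conclusion.** The contradiction is in the current text and should be reconciled. Its main consequence is that the analysed population would not be the one named in the aims. The ceiling is about 10% of patients, 248 of 2476, if the regional share applies to this cohort. The number whose biopsy identifies them is smaller and unknown. The stated power figures are not in question.

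A reader might infer three stronger things that the document does not support.

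- **A biased stenting-versus-radiotherapy hazard ratio.** One can construct a shift: with 15% and 3% non-squamous patients in the two groups and a hazard ratio of 0.7 for those patients, exp(0.12 × ln 0.7) = 0.958, about 4%. All three inputs are invented, and with balanced groups the shift is close to zero. The article gives no histology by site or treatment, so confounding is possible but cannot be quantified.
- **248 patients would be removed.** Patients without a biopsy stay in as presumptive ESCC, so the number removed is lower.
- **Restriction leaves power at 0.99 or above whatever happens.** For stenting versus radiotherapy this depends on the event fraction, which is not stated. With 50% events power is 0.94, although it is only 0.96 with all EC patients included.

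**What to change.** In Statistical methods, replace the single EC sentence with a definition of the ESCC analysis set: patients with histologically confirmed ESCC, plus patients diagnosed clinically without biopsy, excluding those with confirmed non-squamous histology. Use this set for the primary pairwise comparisons and for every result reported as ESCC. Repeat the main analyses in all EC patients as a sensitivity analysis.

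In Eligibility criteria, add a sentence saying that enrolment is open to EC but the ESCC analyses are restricted as above. Enrolment need not change. Bring the abstract and Sample size wording into line.

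Acknowledge as a limitation that non-squamous cancers without biopsy will remain in the set. Their share may vary with access to biopsy, and so by site: Table 1 shows, for example, that pathology is sent out at Tenwek.

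The cost is a sentence or two of text and no new data, because histology is already collected at baseline. The statistical cost is the small loss of power shown in the table.
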